#### Power analysis

As this study is being conducted within a cohort of adolescents, we expect there to be possibly smaller effects [34], which could be due to reduced neurochemical effects, as well as difficulties with subjective mood ratings by the participants. For *N* = 20 participants, a power of 0.97 was calculated (ANOVA, effect for within-subjects factors) to detect small effects (effect sizes of 0.4) with a significance level of α = 0.05 (two-tailed testing, critical F = 3.26). This is in line with previous research showing that mood effects observed after ATD can be rather small in healthy subjects, but possibly more severe in patients affected or vulnerable to depression [35, 36]. Power calculations were performed with G*Power Software, Version 3.1.3 [37]. It is important to note, however, that these calculations are preliminary (conducted before study initiation) and are currently an estimate. The data of this study can be used to inform future larger scale studies. Individuals who are drop-outs or lost to follow-up will be replaced to meet the power calculations.

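### The power of 0.97 quoted for small effects is power for a large effect (f = 0.4) on a three-level test; for a small effect N = 20 gives about 0.14

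*Protocol article*

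**What the plan says.** The Power analysis section gives one calculation. For 20 participants it reports "a power of 0.97 was calculated (ANOVA, effect for within-subjects factors) to detect small effects (effect sizes of 0.4") at a "significance level of α = 0.05 (two-tailed testing, critical F = 3.26"), run in G*Power 3.1.3. It does not name the effect-size metric, the number of measurements, the number of groups or the correlation between repeated measures.

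The same paragraph says that effects in adolescents may be smaller. It adds that "mood effects observed after ATD can be rather small in healthy subjects" but may be stronger in people with or vulnerable to depression, and presents the calculation as consistent with this. Drop-outs are to be replaced so that the calculated power is kept.

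Elsewhere, Study objectives and hypotheses makes the ATD effect on mood, compared with the balanced control, the first objective. Trial design describes Phase A as within-subject. Data preparation and statistical analysis plans repeated-measures ANOVAs with time (three levels) and challenge (ATD or BAL), both within-subject.

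**The concern.** Two things do not fit. First, 0.4 is called small, but on the f scale used for ANOVA power it is the conventional value for a large effect. A paragraph that expects modest effects then reports near-certain power for them. Second, the printed critical value implies two numerator degrees of freedom, whereas ATD versus BAL is a two-level within-subject comparison with one.

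At stake is how the result is read. If the figure is taken at face value, a null ATD–BAL result looks like good evidence against small mood effects, when the trial would usually miss them. A later study planned from this pilot could carry the same misreading into its sample size.

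**Working it through.** **Inputs from the protocol article (Power analysis):** N = 20; effect size 0.4; α = 0.05; critical F = 3.26; power 0.97; within-factor repeated-measures ANOVA in G*Power.

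**Assumed, because the article does not state them:** correlation ρ = 0.5 between measurements and sphericity (ε = 1).

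**Formulae**, with m measurements and k groups:
- noncentrality λ = f² × N × m / (1 − ρ)
- df1 = m − 1; df2 = (N − k)(m − 1)
- power = P(noncentral F(df1, df2, λ) > critical F)

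**Step 1: reproduce the printed figures.** Take f = 0.4, m = 3, k = 2. Then df = (2, 36) and the critical F is 3.259. λ = 0.16 × 20 × 3 / 0.5 = 19.2, and power is 0.972. Both figures match. Alternatives at N = 20:
- k = 1, m = 3: critical F(2,38) = 3.24, power 0.972
- k = 1, m = 2: critical F(1,19) = 4.38, power 0.92
- k = 2, m = 2: critical F(1,18) = 4.41, power 0.92
- m = 4: critical F about 2.77

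**Step 2: could 0.4 be a standardised difference d?** For two means f = d/2 = 0.2. On the three-level test λ = 0.04 × 20 × 3 / 0.5 = 4.8 and power is 0.45, not 0.97. To reach λ = 19.2 with f = 0.2, 1 − ρ would have to be 2.4 / 19.2 = 0.125, so ρ = 0.875. Nothing in the article supports a correlation that high.

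**Step 3: power over the effect-size range**, N = 20, ρ = 0.5, with the range for ρ = 0.3 to 0.7 in brackets:

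| f | Three-level test, F(2,36) | ATD vs BAL, F(1,19) |
|---|---|---|
| 0.40 (large) | 0.97 (0.90–1.00) | 0.92 (0.82–0.99) |
| 0.25 (medium) | 0.65 (0.50–0.87) | 0.56 (0.43–0.78) |
| 0.20 | 0.45 (0.34–0.68) | 0.40 (0.30–0.59) |
| 0.10 (small) | 0.14 (0.11–0.21) | 0.14 (0.11–0.20) |

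At f = 0.1, λ is 0.01 × 20 × 3 / 0.5 = 1.2 for the three-level test and 0.01 × 20 × 2 / 0.5 = 0.8 for the two-level one. On the three-level test, power at f = 0.1 is 0.09 at ρ = 0, 0.30 at ρ = 0.8 and 0.55 at ρ = 0.9. Under the Step 1 settings, 80% power at f = 0.1 needs about 164 participants.

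**Step 4: the ATD–BAL comparison as a paired difference.** Let dz be the mean difference divided by the standard deviation of the within-person differences. Then λ = N × dz², so dz² = 2f² / (1 − ρ), and at ρ = 0.5 dz = 2f. Thus f = 0.4 is dz = 0.8, and λ = 20 × 0.64 = 12.8 as before. A paired t test with n = 20 has power 0.40 at dz = 0.4 and 0.80 at dz = 0.66. These last two figures need no assumed correlation.

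**The case against.** The best defence is that nothing was miscalculated. The 0.97 and 3.26 agree with each other, three measurements match the planned three-level time factor, and moving to the ATD–BAL comparison at the same f and ρ lowers power only from 0.97 to 0.92. The two groups are inferred and could be the two challenge orders described under Blinding procedure and assignment of condition. One group with ε = 0.99 would also give a critical F of 3.258 and power of 0.971. The figure of 0.14 depends on an unstated correlation. The article calls the study a pilot and the calculation preliminary, and allows that effects may be stronger in patients than in healthy people.

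Much of this stands. The fault is in what the number is said to cover, not in the computation. The group structure is an inference. The 0.14 should carry its condition and range. At f = 0.4 the choice of test makes little difference.

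None of it rescues the label. Power at f = 0.1 stays low over any moderate correlation and is only 0.55 even at ρ = 0.9. Stronger effects in patients would be a reason to assume a large effect, not to call 0.4 small. Whatever the two groups represent, a test with two numerator degrees of freedom is not the two-level ATD–BAL comparison. Pilot status lowers what the power must be, but does not make a wrong statement of it right, and the article relies on the figure when it replaces drop-outs to maintain it.

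**Conclusion.** The concern holds. The printed power is correct for f = 0.4, a conventionally large effect, on a three-level within-subject test. It is wrong as a statement about small effects, for which N = 20 gives about 0.14. It is also not the power of the first objective's comparison, which is 0.92 at f = 0.4 and 0.40 at dz = 0.4, with 80% power reached only at dz = 0.66.

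The f-based figures rest on ρ = 0.5 and sphericity. Neither is stated, but together with two groups they reproduce both printed numbers. Departure from sphericity would lower the three-level figures further: at ε = 0.5, power is 0.83 at f = 0.4 and 0.11 at f = 0.1. The conclusion does not depend on what the two groups represent.

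**What to change.** Rewrite the power paragraph and leave N, design and analysis as they are. For example: *With N = 20 and two-sided α = 0.05, the ATD–BAL comparison has power 0.92 for a large effect (f = 0.4, equal to dz = 0.8 at an assumed correlation of 0.5), 0.40 for dz = 0.4, and 0.14 for a small effect (f = 0.1; 0.11 to 0.20 for correlations of 0.3 to 0.7). The smallest effect detectable with 80% power is dz = 0.66.*

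Remove the description of 0.4 as small, and stop using the F(2,36) calculation as the basis for the first objective. If the sponsor wants to keep it for the time effect, it should stand as a separate line with its metric, number of measurements, number of groups and what they represent, correlation and sphericity assumption.

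The cost is wording only. The stated power becomes less favourable, and a null ATD–BAL result should be reported with its confidence interval and not as evidence that small effects are absent.

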#### Trial management

This trial will be managed by the Centre & Discipline of Child and Adolescent Psychiatry, Psychosomatics and Psychotherapy and the Bentley Mental Health Service. The trial will employ several measures to ensure participant safety.

During Phase A, participants will consume the dietary protein amino acid serotonin depletion mixture (ATD challenge). This mixture may cause nausea and vomiting. Additionally, ATD is expected to decrease mood between 5 and 7 h (at maximum). To minimise associated risks with lowered mood, individuals with active suicidal ideation or plans will not be recruited to the study. A study doctor will be available at all times during Phase A to assess and manage these symptoms. Participants will be closely supervised and mood will be monitored frequently on the study days to identify those at risk. Mood will be formally assessed once per hour over 7 hours for each study day (Phase A). Tryptophan replacement (re-feeding) will be given at the end of each study day to normalise substrate availability for 5-HT synthesis. A thorough psychiatric assessment (i.e. mental state, risk assessment and management plan) will be conducted at the beginning and at the end of each study day to clear participants for discharge. The following day, participants will attend a clinical review by a study doctor to assess mood and risk. There will also be close monitoring in Phase B of the study, where participants will be reviewed by the study psychiatrists on a weekly basis for 12 weeks.

Any risk that emerges during the study (i.e. during Phase A or Phase B) will be managed by the research coordinator, who will liaise with the participant’s parent or guardian and arrange for prompt assessment by the participant’s study doctor or the nearest emergency department. All participants will have the research coordinator’s phone number, who will be available during working hours and after-hours of Phase A of the study, and during working hours of Phase B of the study. All participants will be given the Acute Response Team contact details for emergency after-hours support, which is an emergency community-based service that is available 24 h per day. The Acute Response Team will have been briefed about the rationale of this study and will also be regularly informed with regards to the number of participants involved at any point in time. Participants will be provided with a diary card with all relevant contact numbers.

A detailed log will be kept of any adverse events, and this log will be tracked by a Data and Safety Monitoring Committee. Members on this committee are independent of the research team.

The research group has also considered various common and serious adverse events that can occur in adolescents being treated for a major depressive episode with antidepressant medication. In everyday clinical practice, it can sometimes be difficult to be certain whether an adverse event is a result of a specific intervention or due to the depressive disorder. However, this trial will be paused and a review will be undertaken in the event of a completed suicide, suicide attempt, four individuals reporting an increase in acts of deliberate self-harm, three individuals reporting the development of hypomania, and two individuals reporting the development of psychotic–psychosis spectrum symptoms requiring hospitalisation or community-based treatment. Note that these numbers (based on incidence of events relative to percentage of the entire study sample) were estimated from one of the largest available cohorts of comparable patients, the Treatment of Adolescent Depression Study [38]. If patients meet exclusion criteria during the study but require further care, a care plan is in place where participants will have access to care in a community-based mental health setting.

#### Dissemination policy

The final report and publication will be submitted to a relevant academic journal, and findings will be presented in local and international conferences. Furthermore, a summary of the study and its findings will be made available for all participants.

## Discussion

This study may identify a new, simple dietary method to predict treatment response, leading to more targeted pharmacological treatment of adolescents with MDD, and may result in a more rapid treatment response. Children and adolescents may tolerate the ATD/BAL amino acid mixtures better than adults. There have been no serious side effects or complications reported in the studies conducted in minors [12–14, 39]. This study may identify a new, simple dietary method to predict SSRI-related treatment response in terms of serotonergic vulnerability, possibly leading to more targeted pharmacological treatment of adolescents with MDD. In turn, this may lead to a more rapid treatment response and better outcomes. Consequently, adolescents would be able to return to their prior level of functioning earlier, decreasing the overall burden of disease for the individual and allow better integration into the community. Such an approach needs to be confirmed by future larger-scale studies.

### Trial status

This manuscript is based on Protocol Version 11, dated 15th November 2017, and was prepared with reference to the SPIRIT Checklist (Additional file 1).

## Abbreviations

5-HT: serotonin
ATD: acute tryptophan depletion
BAL: balanced control condition
BDI: Beck Depression Inventory
CDRS-R: Children’s Depression Rating Scale - Revised
HDRS: Hamilton Depression Rating Scale
MDD: Major Depressive Disorder
POMS: Profile of Mood States
SSRI: Selective Serotonin Reuptake Inhibitors
TAP: Testbattery for Attentional Performance
TRP: L-tryptophan
